## Background

Chronic obstructive pulmonary disease (COPD), third leading cause of mortality worldwide,^1^ is primarily caused by cigarette smoking in Australia.^2^ COPD often occurs in the presence of multi-morbidity, which is the simultaneous occurrence of two or more chronic conditions; this is a growing concern in a health system focused on single-disease management.^3^ Around 80% of older Australians have multi-morbidity, average prevalence of chronic respiratory disease being 9.5%.^4^

A systematic review of COPD education programs suggests that equipping patients with self-management skills is as important as disease knowledge.^5^ Studies exploring positive effects of chronic disease-management interventions^6^ also underline the lack of studies aimed at empowering patients. Although a recent Cochrane Review^7^ of COPD self-management interventions shows increased health-related quality of life and decreased probability of respiratory-related hospitalisation, similar interventions have not been consistently effective when applied in recent trials.^8–10^ Though interventions aimed at modifying COPD-related health behaviour have great potential, extant literature points to need for self-management programs in primary care.

There is a dearth of interventions involving patients with multi-morbidity, clinicians and other stakeholders, that can be generalisable to other populations.^11^ Patients with multi-morbidity are often excluded from chronic disease-management trials; a Cochrane review^12^ of multi-morbidity interventions found only ten such studies. Our recent qualitative study,^13^ which explored the impact of COPD diagnosis in primary care patients with co-morbidities (co-existing chronic conditions), found suboptimal disease understanding and health-care utilisation. The above evidence demonstrates a need for development and testing interventions to increase self-management capacity in COPD patients with co-morbidities.

Even a brief education session is effective in improving disease knowledge and response to symptoms;^14^ as demonstrated by self-management interventions^10, 15^ on COPD which increased patient self-efficacy. Such programs do not only improve health status and prevent hospital remissions,^16^ but also lead to better patient-provider relationships, self-efficacy and sense of identity.^17^ With no prior study having seemed to focus on improving self-efficacy of COPD patients with co-morbidities in primary care, our study aims to empower these patients by trialling a tailored, practice nurse -delivered self-management program.

## Aims

This pre and post-test pilot study aims to trial the impact and feasibility of a tailored self-management program for primary care COPD patients with multi-morbidity. Our hypothesis is that at six months’ follow-up, participants would have:Better activation in terms of their COPD-related health behaviour.Improved knowledge and self-management capacity of COPD.Increased self-efficacy in terms of their overall health behaviours.

### Inclusion/exclusion criteria

General practices will be eligible if they maintain an electronic database of medical records and employ one or more practice nurse (PN).

Patients will be eligible if they are aged between 40 and 84 years, have a recorded spirometry diagnosis of COPD and at least one other co-morbidity. Exclusion criteria are poor understanding of English and/or cognitive impairment.

### Setting

The study will be conducted in general practices across Sydney, Australia. Practices will be recruited from the UNSW Practice Based Research Network that links practices, which have expressed interest and/or have participated in previous research by [name] and [name]

This is a pre and post-test study comprising a mixed method design, with outcome measures to be collected at baseline and six months’ follow-up. The protocol is summarised in Fig. 1.

**Fig. 1 Fig1:**
[figure not shown]
Study protocol

### Recruitment

An information sheet about the study will be faxed to invite potential practices. [name] will visit interested practices to answer questions and obtain written informed consent from general physician (GP)s and PNs. Practices who do not respond will be followed up after two weeks.

Staff from participating practices will identify potential patients from their database based on inclusion criteria. PNs will then send an invitation letter to eligible patients and remind non-responders after two weeks by telephone. Interested patients will attend visit 1 at their practice, during which [name] will answer questions, obtain written consent, and ask them to complete the baseline questionnaires.

Patient recruitment is deemed feasible as chronic respiratory disease accounts for 12% of patient-GP encounters in Australia, COPD being the 11^th^ most common cause for general practice visits.^18^ Recent COPD casefinding studies in Sydney^19, 20^ have found high disease incidence.

### PN training

PNs will attend a one-day work shop, facilitated by the investigators, which will cover basic pathophysiology of COPD, concept of multi-morbidity, the study design and rationale, COPD self-management based on GOLD^21^ (Global strategy for the diagnosis, management and prevention of COPD) and COPD-X^22^ (Australian-New Zealand COPD guidelines), medication adherence, pulmonary rehabilitation, smoking cessation and principles of motivational interviewing. The workshop aims to equip PNs with knowledge and confidence to understand the intervention, and enable them to tailor and deliver it to patients using an assessment and planning template developed by the researchers. PNs’ competency in delivering the intervention will be assessed using case scenarios, with investigators enacting patients and providing feedback. PNs’ understanding of the intervention and feedback on the workshop will be obtained by means of an evaluation form.

### Intervention

The self-management program of this study is based on the Health Belief Model (HBM),^23^ a widely-tested health education theory explaining human decision-making and subsequent behaviour.

The assessment and planning template for the PN-patient sessions incorporates the HBM’s constructs with strategies for self-management of COPD and co-morbidities. The template includes cues to:COPD knowledge^24, 25^
Relationship between COPD and patients’ co-morbiditiesManagement and prioritisation of their multiple chronic health conditionsManaging flare-ups using a COPD Action Plan^26^
Recommended exercises^27^ and pulmonary rehabilitationProper use of inhalers^28, 29^
Importance of flu and pneumonia vaccination^30, 31^
Medication review and adherenceAdvice on overall health and wellbeingEffects of smoking and benefits of quitting, assistance with quitting and abstinence^32^

Links to relevant resources will be uploaded to a website for the participants’ reference.

During the first PN-patient session (visit 2), individual patient needs will be assessed, and the intervention tailored accordingly. In the following two sessions (visits 3 and 4), PNs will use motivational interviewing^33^ to address barriers faced by patients in managing their COPD in the face of co-morbidities, and work towards optimising health behaviour. The patients will maintain a daily log about their health behaviour in between the education sessions. The logistics of intervention delivery is based on the 5A’s approach,^34^ which is an organisational tool devised to help clinicians Ask, Advise, Assess, Assist and Arrange for their patients’ health behaviour.

Cues to action will be provided to patients in the form of motivational fridge magnets and five follow-up phone calls at monthly intervals by their PNs after the last session. During the course of the intervention, GPs will be notified of situations requiring medical attention (e.g., when treatment needs to be intensified) by the PNs.

### Outcome measures

Impact of the program will be determined by change in patients’ level of self-efficacy between baseline (visit 1) and six months’ follow-up (visit 5), using the Patient Activation Measure (PAM) 13,^35^ a highly-reliable, unidimensional scale of knowledge, skills and confidence for self-management of their health.^36^ The PAM classifies patients across four levels of activation, a significant difference being an increase or decrease of at least one level.

Secondary outcome measures include COPD Knowledge Questionnaire (COPD-Q),^37^ COPD Assessment Test (CAT, an indicator of COPD-related quality of life),^38^ Multimorbidity Illness Perceptions Scale (MULTIPleS, to detect change in perceived impact of multi-morbidity),^39^ a COPD-specific version of the MULTIPleS, Morisky Medication Adherence Scale (MMAS-8)^40^ and accuracy of inhaler technique.^41^ Relationship between objectives, hypothesis, outcomes and measures is outlined in Table 1.

**Table 1 Tab1:** Relationship between objectives, outcomes, measures and hypotheses

Objective	Hypothesis	Outcome	Measure	Visit
To assess the impact of a PN-delivered tailored self-management intervention on COPD patients with multi-morbidity	Tailored self-management education will improve patients’ activation and engagement in their health behaviour, knowledge and self-efficacy of COPD, and increase confidence and skills to manage their multi-morbidity	Change in knowledge, skills and self-management capacity of multiple chronic conditions	Patient Activation Measure (PAM)13^35^	1, 5
		Change in disease knowledge	COPD Knowledge Questionnaire (COPD-Q)^37^	1, 5
		Change in disease related quality of life	COPD Assessment Test (CAT)^38^	1, 5
		Change in perceived impact of multi-morbidity	Multimorbidity Illness Perceptions Scale (MULTIPleS)^39^	1, 5
		Change in perceived impact of COPD in the context of multi-morbidity	COPD-specific version of MULTIPleS	1, 5
		Modified adherence to prescribed medical regimen	Morisky Medication Adherence Scale (MMAS-8)^40^	1, 5
		Accuracy of technique while using inhalers prescribed for COPD	Inhaler device technique checklist^41^	2, 3, 4, 5
To assess the feasibility and sustainability of the PN-delivered self-management education program		Barriers and facilitators to delivery of the intervention, feedback on the program	Semi-structured interviews with GPs and PNs	End of study

COPD chronic obstructive pulmonary disease, PN practice nurse

In accordance with Normalisation Process Theory,^42^ a reliable framework for complex interventions, qualitative feedback will be obtained at the end of the study from participating PNs and GPs to examine feasibility and sustainability of the program.

### Data analysis

Quantitative data will be analysed using Statistical Package for the Social Sciences. Descriptive statistics of responses, expressed as absolute and relative frequencies, will be generated. Categorical data will be analysed by Chi-squared or Fisher’s exact test. Student’s *t*-test for paired samples will be applied for comparing differences in pre and post-intervention outcome measures. Associations will be given as odds ratios.

Qualitative interview transcripts will be coded using NVivo software and thematically analysed by an iterative process.

### Sample size

In accordance with the recommended sample size for feasibility studies demonstrating intervention efficacy in a single group,^43^ our pilot study requires 40 patients, allowing for a 20% drop-out rate^44^ between baseline and six-month visits. This is sufficient to detect a difference in paired measures of patient activation, as demonstrated by a recent study^45^ which used the PAM 13 as an outcome measure, with 85% power at the 5% significance level. A significant difference would be a change between two adjacent stages of the PAM.

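### The paired t-test gives the PAM change only among the roughly 32 of 40 patients expected to complete, and with no control group that figure may be biased in either direction

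*Protocol article*

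**What the plan says.** The study has one group and two measurement times. The Setting section describes the design: "This is a pre and post-test study comprising a mixed method design, with outcome measures to be collected at baseline and six months". The Sample size section bases the number on guidance for "feasibility studies demonstrating intervention efficacy in a single group".

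The Outcome measures section ties the main claim to PAM 13: "Impact of the program will be determined by change in patients", measured at visit 1 and at visit 5. Table 1 lists no other visit for PAM.

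On drop-out, the Sample size section says that "our pilot study requires 40 patients, allowing for a 20% drop-out rate" "between baseline and six-month visits". It claims this is enough to detect a paired difference in activation "with 85% power at the 5% significance level".

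On analysis, the only test that the Data analysis section names for pre/post change is Student's t-test "for paired samples will be applied for comparing differences in pre and post-intervention outcome measures".

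**The concern.** A paired t-test needs both scores. A patient without visit 5 contributes nothing to it, and that patient's baseline PAM goes unused. The article expects one patient in five to be in this position and responds by setting the enrolment number. That keeps the number of pairs up, but the patients who stay may still differ from those who leave.

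In a two-arm trial, similar losses in both arms may partly cancel. Here there is no comparator, so any difference between stayers and leavers passes in full into the estimate. The program asks for three nurse sessions, a daily log and five monthly calls, and the outcome measures knowledge, skills and confidence for self-management. It is reasonable to suspect that staying may be related to activation or to its change, although the article gives no data on this.

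The Discussion lists retention and effect size among the matters that feasibility studies inform. A change that describes stayers only, without a label saying so, is weak evidence for a later trial.

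**Working it through.** **Inputs from the article:** 40 patients including the drop-out allowance, 20% drop-out, 85% power and 5% significance (Sample size); PAM at visits 1 and 5 only (Table 1); paired t-test (Data analysis).

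**Assumptions, because the article gives no figure:** two-sided testing; a true mean change of 0.35 SD (in SDs of the change); the drop-out mechanisms; a visit 1 to visit 5 correlation of 0.5-0.7.

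**1. The plan's own numbers.** 40 × (1 − 0.20) = 32 complete pairs, and 32 / (1 − 0.20) = 40, so the drop-out arithmetic is consistent. The 85% power cannot be reproduced, because a one-level PAM change is given without a points difference or an SD of change. With 32 pairs, 85% power at two-sided 5% (noncentral t) needs a change of 0.547 SD.

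**2. Completers against the whole cohort.** Mean change in all 40 = 0.8 × completer change + 0.2 × leaver change. Let k be the leaver change divided by the completer change:

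| Assumed k | All-40 change / completer change = 0.8 + 0.2k |
|---|---|
| 1 (same change) | 1.00 |
| 0.5 | 0.90 |
| 0 (no change) | 0.80 |
| −1 (equal and opposite) | 0.60 |

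At k = 0 the completer figure is 1/0.8 = 1.25 times the cohort figure. If leavers gained more than completers (k above 1), the completer figure would be too low.

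**3. Direction of the bias.** Simulations of 10^6 patients, true change 0.35 SD, logistic drop-out calibrated to 20%, with the log-odds of leaving falling by 0.5-1.0 per SD of the driver:

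| What drives leaving | Completer change (SD) | Likelihood model on all scores (SD) |
|---|---|---|
| Poor change | 0.45-0.53 | about 0.43-0.50 |
| Low baseline PAM | 0.27-0.31 | about 0.35 |

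The upper end of the first row is 0.52 or 0.53 depending on the run. In the second row completers start higher, and regression to the mean lowers their expected gain.

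**4. Why the model helps in one case only.** With two visits and an unstructured covariance, the likelihood estimate equals the completer change + (b − 1) × (mean baseline of all − mean baseline of completers), where b is the slope of visit 5 on visit 1 among completers. If leavers started lower and b is below 1, both factors are negative and the correction is upward, back to about 0.35. If leaving depends on the unseen change, baseline carries little information about it and most of the bias stays.

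**5. What the no-change analysis gives.** It multiplies the completer figure by 0.8. In the change-driven case this gives 0.8 × 0.45 = 0.36 to 0.8 × 0.53 = 0.42. In the baseline-driven case it gives 0.8 × 0.27 = 0.22 to 0.8 × 0.31 = 0.25, which is too low. It is a stated scenario to read beside the model, not a corrected estimate or a lower bound.

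**The case against.** The strongest reply is that this is a condensed article. Missing-data handling, analysis sets and sensitivity analyses commonly sit in an analysis plan or full protocol that is not shown. The Data analysis section never says complete cases only and never rules out imputation, and a paired t-test is a correct test for one group at two times. This stands in part: the article cannot be faulted for leaving out missing-data detail. The point rests instead on what it does fix, namely a test that needs pairs, an outcome with no intermediate measurement, an expected loss of 20% and no comparator. Nothing in the article points to an analysis that keeps the leavers.

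A second reply is that the direction of bias is unknown. This stands in full. A reader might infer that less engaged patients leave and that the reported change is therefore inflated. The article does not say who leaves or why, and the second row of the simulation table shows that leaving driven by low baseline activation biases the estimate downwards. If leaving is unrelated to change, the completer mean is unbiased.

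A third reply is that a likelihood model does not cure drop-out that depends on the unobserved change. This is also right, and is why the model alone is not enough.

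Finally, this is a pilot, and retention is one of the things it can teach. That lowers the stakes but does not alter what the named test estimates. A reader might also infer that an inflated effect will be used to size the randomised trial. The Discussion speaks only of an evidence base for upscaling and does not say that the point estimate will set a sample size.

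**Conclusion.** The point holds as a statement about what the named analysis estimates. At the expected drop-out, the paired t-test describes about 32 of 40 patients, and no control group offsets any selection. The possible bias is not trivial next to the effect: under the assumed models a true 0.35 SD reads anywhere from 0.27 to 0.53 SD, depending on who leaves. These figures rest on assumed mechanisms, slopes and correlations. They show that either direction is possible and do not predict the study's result.

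The documents do not support a claim of certain upward bias, nor a claim that N = 40 is wrong, since 32/0.8 = 40. A change to the analysis is worth making because it is cheap and the direction cannot be known beforehand.

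**What to change.** - **Main estimate:** estimate the mean PAM change with a simple likelihood-based repeated-measures model, with visit as fixed effect and an unstructured within-patient covariance, on all visit 1 and visit 5 scores of all consented patients. This corrects drop-out related to baseline PAM. Practice random effects and several covariates are too much for 40 patients.
- **Sensitivity analysis:** fix one beforehand that assigns no change to every patient without visit 5, because the model does not correct drop-out that depends on the unobserved change.
- **Description:** compare baseline PAM of completers and leavers.
- **Paired t-test:** report it as supportive, labelled as change among completers.

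The cost is slightly more analysis work and possibly a less favourable estimate. No new data are needed and N = 40 does not change. If an analysis plan not shown here already contains these steps, a sentence in the Data analysis section saying so would be enough.

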### Qualitative process evaluation

Following completion of the program, participating PNs and GPs will be interviewed to gain their feedback. They will be invited via email and written informed consent obtained for recording the interviews, which will be conducted face-to-face by [name] The interviews will be semi-structured with open ended questions covering their experience and opinions regarding the study, as well as feasibility and sustainability of the program. The interview transcripts will be analysed thematically and coded using NVivo software.

## Discussion

To our knowledge, this study is the first aimed at improving self-efficacy of primary care COPD patients with co-morbidities. Primary care is the ideal setting for implementing self-management interventions because early-stage COPD is typically diagnosed and managed in this setting. Our tailored, PN-delivered education program might not only benefit these patients, but could also upskill the PNs’ role in chronic disease management.

According to the UK Medical Research Council framework for complex interventions,^46^ feasibility studies like ours are a vital step for overcoming problems with acceptability, compliance, intervention delivery, participant recruitment, retention and follow-up, and effect size in larger intervention studies. Our study would be enriched by qualitative feedback from patient participants, but this will extend the data collection process and is hence a limitation.

Experience of intervention delivery and uptake from our pilot study would help refine the intervention and shed light on its acceptability and feasibility in day-to-day general practice, providing an evidence base for upscaling the intervention to be tested in a randomised controlled trial. This capacity-building initiative would also promote collaboration and knowledge translation between the various stakeholders.
